### Randomization and Blinding

#### Sequence Generation

Following initial recruitment actions carried out by the clinical service coordinator, the study’s principal investigator will complete the consenting process described above for arm allocation. Participant dyads or triads will then be randomly allocated to an intervention arm A, B, or C, where arm A is usual care, arm B is face-to-face coaching, and arm C is coaching via videoconference (Figure 1). Randomization will occur using a random allocation sequence generated in Microsoft Excel for each reidentifiable participant number, allocated per participant dyad or triad at study enrollment. The sequence will be executed by a blinded research team member who is not directly involved in screening or intervention provision.

#### Allocation Concealment Mechanism

Randomization and study arm allocation will occur prior to baseline measure commencement, and communicated via email or telephone to the participant and principal investigator (who is also the intervention provider) at the conclusion of baseline measure completion. It is not possible to conceal allocation to either party thereafter given that both the intervention provider and participant groups will be aware of either the absence or mode of intervention delivery. Follow-up (T_1_) measures will be completed by the principal investigator.

### Statistical Methods

#### Data Analysis

For the purpose of primary feasibility-related analyses, quantitative data will be analyzed with qualitative analyses relating to individual sessions and therapeutic progress conducted separately. Data analysis will occur according to the data measurement plan described above in Table 1 and Table 2. Descriptive statistics will be used to describe the sample characteristics of parents and children. Recruitment rates will be reported, and retention rates will be evaluated against a predicted rate of 70%-80% in each intervention arm [54]. Goal attainment, measured by performance and satisfaction ratings using the COPM, will provide preliminary evidence for efficacy within the intervention arms. An increase of 2 or more points on a 10-point performance and satisfaction scale in the COPM is considered clinically significant [55].

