**Methods:**

A pilot and feasibility study will be conducted using recommended constructs and associated measures, which will be reported using CONSORT (Consolidated Standards or Reporting Trials) guidance. Participants will be child and caregiver dyads or triads, recruited within 4 months of their child (aged 1-7 years) being referred to one of two services for an ASD assessment in Victoria, Australia. A blinded randomization procedure will be used to allocate participants to one of three trial arms: (1) coaching and support intervention delivered face to face, (2) coaching and support intervention via videoconference, and (3) usual care. Descriptive statistics will be used to describe the sample characteristics of parents and children, inclusive of service access at baseline and follow up. Recruitment rates will be reported, and retention rates will be evaluated against a predicted rate of 70%-80% in each intervention arm. Goal attainment, using the Canadian Occupational Performance Measure, will indicate preliminary evidence for efficacy within the intervention arms, with an increase of 2 or more points on a 10-point performance and satisfaction scale considered clinically significant.

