### Interventions

In the first study arm (A), families will receive usual clinical care. Usual clinical care consists of telephone or email access to an ASD triage and service coordinator during the clinician’s working hours 2 days per week. This clinician is based at a tertiary children’s hospital for service direction and advice as needed, and has relevant expertise in ASD and developmental service delivery at a senior clinician level. Duties include answering service–related queries, offering advice regarding symptom presentation and management, and providing telephone-based counseling as required. Usual care also includes any local service provision that the child or parent may be accessing to address previously identified developmental, behavioral, or health-related issues. These may include, but are not restricted to, access to a local pediatrician, speech pathologist, occupational therapist, or psychologist. Findings from the feasibility study will help to further inform community-based usual care provisions while children await autism diagnostic services.

In addition to usual care, OPC [31] will be carried out with participants in the other two study arms (B and C), differing only by mode of intervention delivery (videoconference vs face-to-face coaching). For the purpose of this study, videoconference is defined as an encounter between the intervention provider and study participants via a live video and audio link.

The intervention arms will be delivered by a clinician who is an experienced pediatric occupational therapist. Occupational therapists are increasingly part of child neurodevelopment assessment and intervention teams, supporting families to identify goals that will assist their child’s functions and participation and improve family quality of life. They are well trained to support families to choose interventions, and to engage children and families in interventions that can help them achieve meaningful or functional goals [36].

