### Outcomes

#### Primary Feasibility Outcome Measures

Feasibility constructs adapted from Bowen et al [34] will be used to guide measures that will be reported following this feasibility trial. These will be measured as described in Table 1. In particular, recruitment and retention rates will be explored and reported, as well as tolerance of randomization and feasibility of collection of the preliminary efficacy measures described in Table 1. Two standardized measures, the COPM [38] and the Measure of Processes of Care-20 [39], will also be used pre- and postintervention to assist with measurement of these feasibility constructs.

**Table 1 table1:** Primary feasibility outcome measures.

Feasibility construct	Recruitment rate	Retention rate	Goal attainment (COPM^a^) [38]	Measure of Processes of Care-20 [39]	Postintervention questionnaire	Time, resource, cost analyses (posthoc)
Acceptability	x	x		x	x	
Demand	x	x				
Implementation	x	x	x			x
Practicality			x	x		x
Adaptation					x	x
Integration Expansion	x	x		x		x
Limited-efficacy testing			x		x	

^a^COPM: Canadian Occupational Performance Measure.

All families will have goals set using the COPM. Although listed in Table 1 as an outcome, the process of goal setting and engagement in the COPM is additionally considered to be an intervention by some researchers and clinicians [40].

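### Preliminary efficacy is read from COPM change within arms, and no contrast with the randomised usual-care arm is stated

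*Protocol article*

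**What the plan says.** The Data Analysis section of the protocol article states: "Goal attainment, measured by performance and satisfaction ratings using the COPM, will provide preliminary evidence for efficacy within the intervention arms". It continues: "An increase of 2 or more points on a 10-point performance and satisfaction scale in the COPM is considered clinically significant". The abstract joins the two in one sentence, where goal attainment "will indicate preliminary evidence for efficacy within the intervention arms, with an increase of 2 or more points on a 10-point performance and satisfaction scale" is tied to clinical significance. Neither place mentions a comparison with usual care on the COPM, and nor does any other section.

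Other sections show that such a comparison is available:

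- Under Primary Feasibility Outcome Measures, "All families will have goals set using the COPM". The same paragraph adds that "the process of goal setting and engagement in the COPM is additionally considered to be an intervention by some researchers and clinicians".
- The COPM and a second instrument "will also be used pre- and postintervention to assist with measurement of these feasibility constructs". That sentence does not say whether usual-care families are re-rated, and Table 2, which lists T0 and T1 for the other instruments, does not include the COPM.
- Under Sequence Generation, families are "randomly allocated to an intervention arm A, B, or C, where arm A is usual care". Here usual care counts as an intervention arm. The Sample Size section does the same, since 18-24 families at 6-8 per arm requires three arms. The Interventions section uses the narrower sense: "The intervention arms will be delivered by a clinician who is an experienced pediatric occupational therapist".

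The Power section says that primary and secondary outcome data will inform power calculations for the full trial. Table 1 lists the COPM among the primary measures. The Discussion limits the efficacy findings to planning that trial.

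**The concern.** A gain from before to after treatment within one arm is not an effect of treatment. Caregivers choose goals because they are problems at that moment, so ratings tend to rise on repetition. Young children mature, and families use the coordinator and local services that make up usual care. The article itself notes that setting goals with the COPM may act as an intervention. All of this can happen in every arm. Only the difference between randomised arms removes, in expectation, what the arms share, and the stated efficacy reading does not use that difference.

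What is at stake is planning. If a within-arm gain is taken as the treatment difference when the full trial is sized, that difference is too large by the amount of shared change, and the trial is too small.

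**Working it through.** **The plan's own precision figure.** The Sample Size section gives a half-width of 16 percentage points for a participation rate of 20% with 24 families. 1.96 × √(0.20 × 0.80 / 24) = 0.160, so it reproduces. It is not in dispute, and it is the only precision figure given. There is none for the COPM.

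**Inputs.** From the article: 2-point threshold; 6-8 families per arm; an even split as the aim; 16 families recruited as of October 2020 (Results); predicted retention 70%-80%. Assumed, because the article gives neither: SD of COPM change 2 (range 1.5 to 2.5), and mean change *m* without any coaching effect, 0 to 1.5 points.

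**Step 1: threshold reached with no coaching effect.** The share of families gaining 2 points or more is 1 − Φ((2 − m)/SD).

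| m | SD 1.5 | SD 2 | SD 2.5 | Expected among 16 coached families, SD 2 |
|---|---|---|---|---|
| 0 | 9.1% | 15.9% | 21.2% | 2.5 |
| 1 | 25.2% | 30.9% | 34.5% | 4.9 |
| 1.5 | 36.9% | 40.1% | 42.1% | 6.4 |

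For *m* between 0 and 1 the range is 9% to 35%. The mean of an arm is less easily misread. At SD 2, an arm of 8 averages 2 points or more with probability 1 − Φ((2 − m)/(2/√8)), which is 0.2% for m = 0, 8% for m = 1 and 24% for m = 1.5. The article does not say whether the threshold will be read on families or on arm means.

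**Step 2: consequence for sizing.** Normal approximation, SD 2, two-sided 5%, 80% power: n per arm = 2 × (1.960 + 0.842)² × SD² / difference².

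- Difference taken as 2 points: 2 × 7.85 × 4 / 4 = 15.7, so 16 per arm.
- If 1 of those 2 points is shared by all arms, the true difference is 1 point: 2 × 7.85 × 4 / 1 = 62.8, so 63 per arm.

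That is a fourfold shortfall under these assumptions.

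**Step 3: precision of the randomised contrast.** The 95% half-width is t(0.975, n₁ + n₂ − 2) × SD × √(1/n₁ + 1/n₂), with coaching arms B and C pooled against A.

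- 16 vs 8 (full target of 24): 2.074 × 2 × √(1/16 + 1/8) = 1.80 points (1.35 to 2.25 for SD 1.5 to 2.5).
- 11 vs 5 (the 16 families recruited, assuming a near-even split): 2.145 × 2 × √(1/11 + 1/5) = 2.31 points (1.74 to 2.89).
- 8 vs 4 (12 completers, 75% of 16): 2.228 × 2 × √(1/8 + 1/4) = 2.73 points (2.05 to 3.41).

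The contrast can be estimated, but at the numbers recruited its half-width exceeds 2 points when the SD is 2.

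**The case against.** The strongest reply is that this is a feasibility study. Efficacy is called preliminary, its use is confined to planning, and a condensed article may leave estimand, pooling and covariates to an analysis plan that is not shown. The article also discloses that goal setting may act as an intervention and says that usual care will be described. This lowers the severity. It does not remove the point, because the article states how efficacy will be read, twice, and that statement is the fault. The absence of a significance test is reasonable at this size.

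Three stronger readings are tempting and are not supported:

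- *That COPM change will be examined only in the coaching arms, so the control is discarded.* Sequence Generation and Sample Size count usual care as an intervention arm, so change may be reported in all three. Even then, three within-arm readings are not a contrast.
- *That 2-point gains will decide whether the full trial goes ahead or will be declared a positive result.* No section sets a COPM progression rule. The Power section says only that outcome data will inform the calculation; those data might supply just an SD.
- *That comparison with arm A would isolate the coaching effect.* Under Allocation Concealment Mechanism, T1 measures are completed by the principal investigator, who delivers the coaching and knows the allocation, as do families. The contrast keeps that bias.

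**Conclusion.** The point holds as a matter of stated inference. Within-arm COPM change is presented as preliminary evidence for efficacy, and no contrast with the randomised usual-care arm is stated under either meaning of *intervention arms*. The size of the distortion equals whatever change is common to all arms, which the article does not allow one to estimate. The 9% to 35% figure and the sizing illustration therefore rest on the assumed SD and shared change. Harm to the next trial is conditional on a within-arm gain being used as its treatment difference. Severity is moderate: it should be fixed, but the feasibility aims do not depend on it.

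**What to change.** - Define *intervention arms* once and use the term in that sense throughout.
- State that the COPM is rated at T0 and T1 in all three arms.
- Report mean change and the proportion gaining 2 points or more in each arm, labelled descriptive. Keep the 2-point figure as a description of individual change only.
- Give (B + C) minus A as the preliminary efficacy estimate, adjusted for baseline COPM where numbers allow, with a 95% confidence interval and no significance test.
- State as a limitation that T1 measures are completed by the unblinded intervention provider, and that the contrast does not correct for this.

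The cost is a few sentences and one small model. Goals are already set in arm A and T1 is already planned; if COPM re-rating in arm A was not intended, it adds a short task at that visit. The real price is a wide interval in place of an apparently favourable within-arm result.

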#### Power

Data gathered from this feasibility study will be used to calculate recruitment and retention rates. Primary and secondary outcome measure data will be used to inform future power calculations, which are required to estimate appropriate recruitment numbers for a fully powered RCT aimed at gathering efficacy data.

### Ethics Approval and Consent to Participate

All study attributes will be carried out in line with the National Health and Medical Research Council Act 1992, and following approval from the RCH Human Research Ethics Committee. Ethical approval was granted by The RCH Research Ethics and Governance Department in September 2018 (HREC 38154A), spanning all elements detailed in this protocol to take place across the campus organizations of The University of Melbourne, The Murdoch Children’s Research Institute, and the RCH, Melbourne. Only families who provide explicit consent to participate with a signed consent form will be eligible for this study.

## Results

The trial has concluded recruiting families of children referred for an ASD assessment throughout 2019. It remains under ethical approval and will continue throughout 2020. As of October 2020, 16 families have been recruited to the study.

Results will be reported according to CONSORT guidance [56] following the conclusion of this study. Feasibility findings as described above will be reported as primary outcomes. Preliminary efficacy findings will be reported as primary and secondary outcomes, as described in Tables 1 and 2.

## Discussion

To our knowledge, this is the first study measuring the feasibility of OPC via two different parallel modalities for families awaiting ASD assessment. Given the lag time between identification of concerns and assessment that many families experience, identification of an intervention that addresses primary family concerns in this interim period is warranted

Uncertainty exists in relation to optimal feasibility study methodology when testing new interventions or existing treatments for alternative populations. In recent years, efforts have been made to make recommendations regarding pilot and feasibility studies; however, there remains no consistent approach as to how such studies should be conducted and measured [34,54]. As such, we have incorporated a diverse range of feasibility constructs and outcomes to ensure comprehensive evaluation that can inform future trial planning.

Additional strengths of this study include broad participant inclusion, consideration of alternative modes of service delivery in comparison with usual care, and incorporation of fidelity measures. Exclusion criteria have been kept to a minimum to allow the research team to have a broad sense of the nature of families who are interested in, and able to complete, the intervention. In particular, the availability of an interpreter service is aimed at encouraging participation of families for whom English is their second language. Moreover, the study will measure the feasibility of two different modes of service delivery in comparison with usual care, and explore the tolerance of randomization to these study arms. Finally, the fidelity of the intervention will be measured using a published tool as described previously [37].

In spite of these strengths, there are several limitations to consider during interpretation of the feasibility results. In line with suggested general pilot and feasibility methodologies, the sample size will be smaller than that used in full-scale clinical trials or efficacy studies. Preliminary efficacy findings will only be used as an aid to plan for a future RCT. Nevertheless, the planned sample size is consistent with similar studies that have focused on coaching, telehealth, or videoconference interventions [25,52], and is appropriate to address the research aims.

Although a broad participant recruitment strategy has been formulated, occurring across two sites, data collection and face-to-face coaching sessions will be carried out at only one site (RCH). This may prove to be a limitation in either recruitment or retention. Additionally, given that these sites offer publicly funded services, the participant sample has the potential to be biased, likely excluding families for whom a prompt, private service for assessment was accessible. Such predictions are in line with previous research in publicly funded developmental assessment services in Australia [57], in which the researchers found that families accessing such services were more likely to have a lower sociodemographic status or have English as a second language when compared to the general population. Given our plan to include families who may require interpreting services, translation and tool validation–related issues will mean that the secondary feasibility measures will need to be interpreted with caution. A future RCT will likely require coaching to be delivered at multiple sites to maximize the recruitment and generalizability of results.

Finally, all families who are participating in the study, regardless of study arm allocation, will continue to receive usual care. This is likely to be highly variable given that service access depends on family resources, geographical location, and other factors not yet known to the research team. Usual care will be described and considered in relation to relevant findings.

This study is the first step toward addressing an evidence gap by exploring potential interventions that can support families when on an ASD assessment waiting list. Findings of this study could inform the best care for families and children on waiting lists for other presentations, catering to an ongoing issue in health systems internationally.

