Occupational Performance Coaching (OPC) is an occupation-informed intervention developed to address the functional support needs of children and families [23]. OPC is theoretically informed by occupation and family-centered practice, along with ecological models of child health and well-being. This approach involves supporting families to generate goals relating to themselves, their child’s functioning, or the functioning of their family as a whole. The therapist, through a series of interactive semistructured interview sessions, then provides opportunities for reflection, sharing of knowledge, and the development of attainable actions. Performance analysis, strategy generation, and resource identification take place collaboratively, and actions are reviewed in subsequent sessions until goals are reached. Effectiveness of this intervention holds promise and continues to be evaluated [28-30]. To date, OPC has been typically examined in face-to-face sessions around 60 minutes in length, with a range of dosages between 2 and 12 sessions [31]. However, OPC has not yet been tested specifically with families of children waiting for ASD assessment, nor have the modes of treatment delivery, including delivery via telehealth or videoconference modalities, been compared concurrently within the same study. These modalities require particular exploration given social distancing challenges brought about as a result of the COVID-19 pandemic.

In novel clinical trial applications, the importance of initial feasibility testing and reporting has been reiterated in recent years [32,33]. Therefore, the aim of this study is to assess whether a small number of coaching sessions is feasible for families and has potential to address family needs while waiting for ASD assessment. The intervention’s acceptability, practicality, expandability, and demand, as well as the types of needs in the local context that require interventions [34] will be examined. Such explorations are essential to inform a future randomized clinical trial protocol, with risk of bias minimization and appropriate methodological rigor.

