## Methods

### Trial Design

Trial design elements are described in line with CONSORT (Consolidated Standards of Reporting Trials) guidance for pilot and feasibility studies [35]. This study is a pilot RCT and feasibility study, with a focus on feasibility outcomes, following participant allocation to one of three parallel study arms inclusive of a usual care group. The study flow is detailed in Figure 1.

Allocation ratios will be determined by the randomization process outlined below with an aim of obtaining an even number of participants allocated to each study arm.

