### Sample Size

A pragmatic sample size of 18-24 families is sought to allow for 6-8 participants randomized to each intervention arm. These numbers are in line with similar pilot and feasibility studies in relation to coaching, including those delivered via videoconference or telehealth [25,52]. Based on clinical and research expertise across the team, this number was considered to be sufficient to inform protocol planning related to a future RCT, and to satisfactorily meet the requirements for obtaining all research aims. With a sample size of 24, we will be able to predict a participation rate of 20% to within a 95% CI of 16% [53].

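### Feasibility of the two coaching modes is promised relative to usual care, but the stated analysis rules contain no between-arm contrast

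*Protocol article*

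**What the plan says.** Two places in the Protocol article raise the expectation of a comparison. The Introduction, describing earlier work on Occupational Performance Coaching, says "nor have the modes of treatment delivery, including delivery via telehealth or videoconference modalities, been compared concurrently within the same study". The Discussion, listing strengths, says "the study will measure the feasibility of two different modes of service delivery in comparison with usual care". Trial Design supplies three parallel randomised arms, one of them usual care, "with an aim of obtaining an even number of participants allocated to each study arm".

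Data Analysis gives two numeric rules:

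- Retention: "retention rates will be evaluated against a predicted rate of 70%-80% in each intervention arm".
- Goal attainment on the COPM: the ratings "will provide preliminary evidence for efficacy within the intervention arms", and "An increase of 2 or more points on a 10-point performance and satisfaction scale in the COPM is considered clinically significant".

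Recruitment rates are to be reported, with no yardstick. Under Primary Feasibility Outcome Measures, the article says that families in every arm set COPM goals, and it concedes that some regard this goal setting as an intervention in itself. Near its end the Discussion says that usual care will be described and taken into account alongside the findings. It specifies no contrast.

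**The concern.** A comparison needs a quantity that involves both arms. Each stated rule uses one arm and a fixed outside figure. Two arms can fall on different sides of 70% while the randomised difference between them is compatible with a large advantage for either. Placing two single-arm results next to each other does not show that uncertainty.

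The gap matters most against usual care. COPM change within a coaching arm mixes any effect of coaching with the effect of setting goals, the passage of time and regression to the mean. The usual-care arm shares those components, so the difference between arms is what separates them. If usual-care COPM ratings have no stated use in a contrast, the main benefit of randomising to that arm is lost for this outcome. The future trial would then be planned from uncontrolled change scores.

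**Working it through.** **Inputs.** 18-24 families in three arms, so 6-8 per arm (Sample Size: "A pragmatic sample size of 18-24 families is sought to allow for 6-8 participants randomized to each intervention arm"). Retention of 70%-80% (Data Analysis). COPM threshold of 2 points (Data Analysis). The documents give no SD for COPM change, so 1.5, 2.0 and 2.5 are assumed.

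**1. The plan's own precision figure.** Sample Size states "With a sample size of 24, we will be able to predict a participation rate of 20% to within a 95% CI of 16"%. The half-width is 1.96 × √(0.20 × 0.80 / 24) = 0.160, so the 16% reproduces. It concerns one proportion in the whole sample and does not bear on any difference between arms.

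**2. Which stated rules use a second arm?**

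| Stated rule | Compared with | Uses another arm? |
|---|---|---|
| Retention, per arm | external 70%-80% | no |
| COPM change, within arms | 2 points | no |
| Recruitment | nothing; study-level | no |

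The article is not consistent about what an intervention arm is. In Sample Size the term must cover all three arms (3 × 6 = 18, 3 × 8 = 24), whereas Interventions separates usual care from the coaching arms. On the narrow reading usual care has no retention yardstick and its COPM scores have no stated use. On the broad reading it has its own yardstick. Neither reading produces a between-arm contrast.

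**3. How far one family moves the per-arm result.** With 8 per arm, 5/8 = 62.5% is below 70% and 6/8 = 75% is inside the range. With 6 per arm, 4/6 = 66.7% is below and 5/6 = 83.3% is above. The exact 95% CI for 6/8 is 35% to 97%.

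**4. Precision of a retention difference.** Newcombe interval: for d = p1 - p2 with Wilson limits (L, U), the lower limit is d - √[(p1 - L1)² + (U2 - p2)²] and the upper limit is d + √[(U1 - p1)² + (p2 - L2)²].

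Wilson limits: 5/8 (0.306, 0.863); 6/8 (0.409, 0.929); 4/6 (0.300, 0.903); 5/6 (0.437, 0.970).

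- 5/8 v 6/8: lower = -0.125 - √(0.319² + 0.179²) = -0.491; upper = -0.125 + √(0.238² + 0.341²) = +0.291.
- 6/8 v 6/8: 0 ± √(0.341² + 0.179²) = ±0.385.
- 4/6 v 5/6: lower = -0.167 - √(0.367² + 0.137²) = -0.558; upper = -0.167 + √(0.237² + 0.397²) = +0.295.

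The simple formula 1.96 × √(2p(1 - p)/n) gives half-widths of 45-52 points at n = 6 and 39-45 points at n = 8, for p between 0.80 and 0.70.

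**5. Precision of a COPM difference.** Half-width = t × SD × √(2/n), with t = 2.228 (10 df) at n = 6 and 2.145 (14 df) at n = 8. For pooled coaching (16) against usual care (8) it is t × SD × √(1/16 + 1/8), with t = 2.074 (22 df).

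| Assumed SD | 6 v 6 | 8 v 8 | 16 v 8 |
|---|---|---|---|
| 1.5 | 1.93 | 1.61 | 1.35 |
| 2.0 | 2.57 | 2.14 | 1.80 |
| 2.5 | 3.22 | 2.68 | 2.25 |

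These are of the same order as the 2-point threshold. A difference can be estimated and reported, but it cannot carry a test.

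**The case against.** The strongest reply has four parts.

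First, a reader might infer that families are randomised in order to set the modes against each other. The documents do not say so. The Discussion sentence promises each mode relative to usual care. Mode against mode appears only as a gap in earlier work, and the specific aims are feasibility and planning of a future trial. This stands, and it is why usual care is the main contrast here.

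Second, a reader might conclude that no comparison will ever be made. That cannot be known. The article is condensed, an analysis plan may exist, and arm-by-arm description is normal in a pilot. This also stands, as a limit on the claim. It does not remove the point, because the article goes beyond silence: it states the yardstick (an external figure) and the scope (within arms), and these do not fit the comparison that it lists as a strength.

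Third, a reader might treat 70%-80% as a pass mark that selects a mode. The article states no such go/no-go or selection rule, and it already foresees both modes in the future trial. Nor is every stated measure arm-specific, since recruitment belongs to the study as a whole.

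Fourth, intervals this wide tell planners little, and the Discussion already limits the efficacy findings to planning. True, but planners need to see that width, and single-arm summaries do not show it.

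**Conclusion.** The point holds in limited form. The rules stated in Data Analysis contain no between-arm contrast, while the Discussion claims feasibility relative to usual care and the Introduction cites the missing concurrent comparison of modes. It is a mismatch between claim and stated analysis. It is not evidence that a comparison will be omitted, nor that the article declares either mode better.

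On size: with equal observed retention of 75% in two arms of 8, differences up to about 38 points either way remain possible. The simple half-widths run from 39 to 52 points over the planned arm sizes and the predicted retention range. The data therefore cannot rank the modes. The retention figures assume the planned 6-8 per arm. With the 16 families reported as recruited by October 2020, about 5 per arm, they would be wider. The COPM figures rest on assumed SDs of 1.5-2.5.

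**What to change.** In Data Analysis, state that between-arm differences will be reported with 95% CIs and without hypothesis tests for retention, COPM change, the Measure of Processes of Care-20 and the scored Table 2 scales, with scores adjusted for their T0 value. Make coaching minus usual care the main contrast, and say whether it is for each mode or for the modes pooled. Give videoconference minus face-to-face as a descriptive contrast. Leave out the self-designed history questionnaire, for which no score is described, and note that the Social Responsiveness Scale covers only children older than 2.5 years.

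Confirm that usual-care families rate the COPM and the Measure of Processes of Care-20 again at T1. The article calls these time points pre- and postintervention, which is unclear for an arm without the intervention.

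Keep 70%-80% as a description of each arm. In the Discussion, say that at 6-8 families per arm retention differences of roughly 40 points or more either way cannot be excluded, so the modes cannot be ranked.

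The cost is a few lines and one table from data that the article already plans to collect, subject to that T1 check. The downside is wide intervals and a more modest comparison claim. The sample size does not change.
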